### Health economics

Within trial economic analysis of direct resource costs and health outcomes will be conducted on an intention to treat basis. A health service perspective will be adopted for measuring and valuing health care utilisation. Using a case-mix approach, we will estimate acute hospital one-year cumulative costs based on the index episode and subsequent events defined in the MACE composite clinical endpoint. No discounting of direct resource costs will be conducted as the time horizon will be limited to one year for within trial analysis.

Survival times will be adjusted using preference or utility weights assigned to each of the events in the MACE to calculate quality adjusted life years (QALYs). The primary treatment effect in the economic analysis will be estimated using an individual level regression model for average (mean) incremental costs and incremental QALYs. The model will consider the joint distribution of costs and QALYs using a general specification that will allow for different parametric and conditional distributions. We also plan to use a Bayesian model with minimally informative priors for means and large variances, following the general framework outlined by Baio [29]. Model parameter uncertainty will be addressed using probabilistic sensitivity analysis summarised using the cost-effectiveness acceptability curve. The heterogeneity of economic treatment effects will be assessed using pre-defined strata on age and people with diabetes.

Longer run modelling will estimate the distribution of costs and QALYs calculated over the expected patient lifetimes. A microsimulation model will be calibrated using information gained from the within trial analysis of cost-effectiveness combined with additional data from (i) trials and observational studies reporting longer run costs, survival and health related quality of life following RIPC and (ii) expert beliefs on the distributions of parameters where information is less readily available. The structural uncertainty in the long run model will be addressed using model averaging methods [30].

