### Data at 1 year

General practitioners will be contacted 1 year following randomisation to ascertain whether participants have died or suffered myocardial infarction or cerebrovascular accident. The national Hospital In-Patient Episode (HIPE) database will be interrogated for hospital admissions and patient status in the year since surgery.

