#### Primary safety endpoint

The intervention under investigation carries a theoretical risk of causing acute upper limb ischaemia or an upper limb deep vein thrombosis. Such an event has not been reported by any of the phase 1 and 2 trials of RIPC in cardiac patients. In addition, there is a theoretical risk of minor adverse events such as upper limb bruising. The primary safety endpoint will again be a composite of major life- or limb-threatening adverse events that could be attributed to the preconditioning stimulus. The components are:Acute upper limb ischaemiaAcute upper limb deep vein thrombosis

The components of the primary safety endpoint are defined as follows:Acute upper limb ischaemia, which is defined as the development of ischaemia in the arm used for the preconditioning stimulus requiring systemic anti-coagulation, radiological intervention or surgical intervention; andAcute upper limb deep vein thrombosis, which is defined as the development of thrombus within the subclavian, axillary or brachial vein confirmed in duplex ultrasound and in the same arm as used for the RIPC stimulus.

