**Table 2 Tab2:** **Definitions of other post-operative complications**

Respiratory failure	Unplanned initiation of assisted ventilation (CPAP or IPPV)
Transient ischaemic attack	New onset neurological deficit with lateralising signs, which resolves within 24 hours without evidence of cerebral bleeding or infarction on imaging and confirmed by a stroke physician or neurologist
Vascular graft occlusion	Occlusion of prosthetic or vein graft confirmed by imaging within 30 days of surgery
Wound infection	Erythema, purulent discharge, pyrexia, positive pathogenic organism on culture
Chest infection	Cough, dirty sputum, pyrexia, positive sputum culture +/−pathogenic organism on sputum culture
Urine infection	Pyrexia, leucocytosis, pathogenic organism on urine culture
Abdominal infection	Intra-abdominal abscess formation confirmed on CT scan or at laparotomy
Other sepsis	Sepsis due to any cause other than those listed above for example, line infection
Prolonged ileus	Absence of bowel function requiring the initiation of nutritional support
Pulmonary embolus	Confirmed radiologically or at autopsy
Deep vein thrombosis	Confirmed radiologically or at autopsy
Limb ischaemia	Compromised circulation in a limb requiring a revascularisation procedure within 30 days of surgery
Major limb amputation	Amputation of a limb due to unsalvageable critical ischaemia within 30 days of surgery
Renal infarction	New renal infarction on post-operative imaging
Renal impairment	Post-operative ≥20% increase in serum creatinine from pre-operative baseline

CPAP – continuous positive airway pressure; IPPV – intermittent positive pressure ventilation.

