**Table 3 Tab3:** **Acute kidney injury criteria**

**AKI grade**	**Creatinine criteria**	**Urine output criteria**
1	Rise > 26.4 μmol/L or 150 to 200% of baseline	<0.5 ml/kg/h for >6 h
2	Rise of 200 to 300% of baseline	<0.5 ml/kg/h for >12 h
3	Increase of 300% or creatinine >354 μmol/L with acute rise of at least 44 μmol/L	<0.3 ml/kg/h for >24 h or anuria for 12 h

Legend: Table summarising acute kidney injury criteria.

AKI – acute kidney injury.

### Proposed composite Primary Efficacy Endpoint for Phase 3

The proposed primary efficacy endpoint is a composite Major Adverse Clinical Event (MACE). The selected endpoints represent common, life-threatening complications of major vascular surgery. Ischaemia-reperfusion injury plays a significant role in these events, and thus, it is biologically plausible that RIPC would reduce the frequency of these events. The components are all strictly defined. The occurrence of any of these events in a patient will be classified as a MACE. The occurrence of multiple events in a single patient will also be classified as a single MACE for the purposes of trial analysis. The components of the primary efficacy endpoint are as follows:Cardiovascular deathMyocardial infarctionCerebrovascular accidentRenal failure requiring renal replacement therapyMesenteric ischaemia requiring intervention or biopsy-proven ischaemic colitis

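### After the index episode, the economic analysis costs and weights only MACE events, so non-MACE readmissions add no cost and non-fatal non-MACE harms lose no QALYs

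*Protocol article*

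**What the plan says.** The Health economics section of the protocol article sets the perspective first: "A health service perspective will be adopted for measuring and valuing health care utilisation". It then fixes what is costed: "we will estimate acute hospital one-year cumulative costs based on the index episode and subsequent events defined in the MACE composite clinical endpoint". For the QALY it says: "Survival times will be adjusted using preference or utility weights assigned to each of the events in the MACE". The within-trial horizon is one year.

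MACE is defined under Proposed composite Primary Efficacy Endpoint for Phase 3. It has five components: cardiovascular death, myocardial infarction, cerebrovascular accident, renal failure requiring renal replacement therapy, and mesenteric ischaemia. The renal component counts only if replacement therapy starts within 30 days of surgery.

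Three other sections matter here:

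- Primary safety endpoint covers acute upper limb ischaemia and upper limb deep vein thrombosis, described as "major life- or limb-threatening adverse events that could be attributed to the preconditioning stimulus". Upper limb ischaemia is defined by the treatment it needs: "requiring systemic anti-coagulation, radiological intervention or surgical intervention".
- Table 2 lists 15 other complications, among them graft occlusion, several infections, major amputation and limb ischaemia. Limb ischaemia is defined as "Compromised circulation in a limb requiring a revascularisation procedure within 30 days of surgery".
- Data at 1 year says that the national HIPE "database will be interrogated for hospital admissions and patient status in the year since surgery". It does not limit this to MACE causes.

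**The concern.** An analysis from the health service's side should reflect the hospital care that patients use. The written rule covers the index episode in full, then only the events chosen as the phase 3 efficacy composite. The figure it produces is therefore not the one-year acute hospital cost, although the admissions needed to calculate that cost are to be obtained.

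The utility rule is narrower still. For costs, the index episode at least catches harms treated in the first stay. For QALYs there is no such cover: an event outside the composite has no weight whenever it occurs, unless the patient dies and survival time is shortened. A QALY built this way cannot register a non-fatal event from the trial's own primary safety endpoint.

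The long-run model is calibrated partly on the within-trial result, so the restriction may carry into the lifetime estimates. The planned probabilistic sensitivity analysis varies parameter values; it does not bring excluded events back in.

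**Working it through.** **1. Apply the written rule to each kind of event.** The article states no economic result that could be reproduced, so the check sets the costing and utility rules beside the event definitions.

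| Event (section) | Cost if treated in the index stay | Cost if it leads to a later admission | Utility weight |
|---|---|---|---|
| MACE component (Proposed composite) | Yes | Yes | Yes |
| Upper limb ischaemia or deep vein thrombosis (Primary safety endpoint) | Yes | No | None |
| Graft occlusion, limb ischaemia, infection (Table 2) | Yes | No | None |
| Major amputation (Table 2) | Yes | No | None |
| Renal replacement started after day 30 | Yes, if still in the index stay | No | None |
| Non-cardiovascular death | Yes | No | None, but survival time is shortened |

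The cost gap is confined to the third column. The utility gap applies to every non-fatal event outside MACE.

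**2. Compare with the data to be collected.** HIPE admissions over the year are planned without restriction by cause, so the material for costing later admissions would be in hand. The Table 2 definitions of graft occlusion, limb ischaemia and amputation stop at 30 days. Later events of these kinds would therefore be seen only as HIPE admissions.

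**3. Size, under assumptions.** The documents give no unit cost, utility or non-MACE readmission rate. Let d be the between-arm difference in the proportion of patients with an omitted event, c the cost of a readmission in units of one index stay, and u the QALY loss per event. Then:

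- omitted incremental cost per patient = d × c
- omitted incremental QALY per patient = d × u

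For illustration, assume d between 0.02 and 0.05, c between 0.5 and 2, and u between 0.02 and 0.10.

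- Cost, low end: 0.02 × 0.5 = 0.01 index-stay costs per patient.
- Cost, high end: 0.05 × 2 = 0.10 index-stay costs per patient.
- QALY, low end: 0.02 × 0.02 = 0.0004 per patient.
- QALY, high end: 0.05 × 0.10 = 0.005 per patient.
- If d = 0, both are zero.

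The sign follows the sign of d, which the documents do not determine. The omitted events for cost (later admissions) are also a narrower set than those for the QALY (any non-fatal non-MACE event), so the two values of d need not agree.

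**The case against.** **Perspective and scope are different things.** A health service perspective says whose costs count, not which events are costed. Limiting costs to outcomes that the intervention might plausibly affect is a recognised choice and avoids noise from unrelated admissions in a trial of 400 patients. This stands as a reason to keep a MACE-only analysis. It does not make that analysis a measure of health care utilisation in general, which is how the section introduces it. Nor does it explain leaving out the harms that the protocol itself regards as attributable to the cuff.

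**The article condenses a fuller plan.** Mapping of HIPE codes and the sources of utility values may well sit elsewhere and are not at issue. The restriction to MACE, however, is stated in the article as the rule.

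**A reader might infer that RIPC's own harms are costed at zero.** The text does not support that. The index episode is costed without restriction to MACE, and the cuff is applied immediately before surgery, so arm ischaemia or thrombosis may well be treated in that stay.

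**A reader might also infer that the results are tilted towards RIPC**, because expected benefits are counted and possible harms are not. The documents do not show this. The primary safety section calls the arm events a theoretical risk and reports none in the early cardiac trials. Most of the other omitted events are complications of vascular surgery rather than of the cuff. Possible benefits are omitted too: Table 2 includes respiratory failure and renal impairment, and the Background cites small trials in which RIPC lowered pulmonary or renal injury markers. If RIPC reduced such events, leaving out their later costs and utility losses would work against it.

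**The lifetime model has other inputs.** It also draws on external studies and expert opinion, and uses model averaging for structural uncertainty. The within-trial restriction is therefore only one influence on it.

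**Conclusion.** The point holds in a limited form. As written, readmissions outside MACE add no cost, and non-fatal events outside MACE cause no QALY loss. The latter include the primary safety endpoint, major amputation and renal replacement started after day 30. This does not match the stated health service perspective or the planned one-year HIPE search.

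The effect on the between-arm difference is unknown in size and direction. The ranges in the working rest entirely on assumed inputs and show only how the omission scales. No bias in favour of RIPC is established. The economic analysis is not listed among the trial's endpoints, and the primary troponin comparison is untouched. This is a cheap improvement to a supporting analysis.

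**What to change.** In Health economics, base one-year acute hospital costs on the index episode plus all HIPE admissions from surgery to one year, and keep the MACE-only costing as a sensitivity analysis. Extend the utility decrements to the two primary safety events, to major amputation, and to renal replacement started at any time in the year.

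The price is extra costing work on admissions data already planned, utility values for a few more events, and somewhat wider cost intervals from unrelated admissions. The retained MACE-only analysis shows how much those admissions matter. One practical check: HIPE records in-patient episodes, and the planned one-year contact with general practitioners asks about death, infarction and stroke. Late renal replacement without an in-patient episode might be missed by both, and one added question to the general practitioner would cover it.

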### Qualitative data analysis

Each interview will be transcribed verbatim, following which, the transcript will be reviewed by the researchers for accuracy. Each interview will be ‘openly coded’ (to allow development of categories of concepts, without making any prior assumptions). The researcher will analyse half the interviews first to identify common codes for each group of respondents. These coded transcripts will be reviewed by a second researcher to ensure the interviews are coded correctly and consistently and the codes identified by the researcher were the same as those identified by the expert. The second half of the transcripts will be consequently added to the analysis one-by-one allowing for the monitoring of data saturation.

For the purpose of this research, thematic analysis will be used to analyse qualitative data. This approach has many benefits for studies such as this, which are interpretive in nature, as it is a ‘method for identifying, analysing and reporting patterns (themes) within data’ [31]. The process of thematic analysis is concerned with the basic to advanced encoding of data, which are subsequently developed to themes. Themes are described as ‘patterns found in the information’ that can be developed in an inductive manner from raw information but also deductively from prior/existing research and knowledge. This flexible approach can also be seen in how themes identified at one level can help the researcher describe their observations and at a more advanced level allow the researcher to interpret aspects of the phenomenon under study [31].

Qualitative data analysis will be systematic and organised in order to easily locate information within the data set when tracing results, providing examples in context [31]. The qualitative research software Nvivo v8 will be used to facilitate the coding of this data. Such research software allows the researcher to manage, shape and make sense of unstructured information; it also facilitates the complex organisation and retrieval of data (www.qsrinternational.com). The analysis will follow a ‘5-Step Analysis’ approach whereby data is reviewed, examined, coded, themes generated and defined [31]. To achieve validity in the coding/analysis of data, two reviewers will code data independently and inter-rater reliability measures will be computed based on this coding. Coding consistency will be maintained throughout the coding process and will be reviewed by regular meetings between researchers and principal investigator. The findings will be compared with other study findings (validity and credibility). The researchers will present the findings to participants to determine if the study findings reflect their experience of the topic under study (member checking). Illustrative quotes will be used to emphasise points made by the participants.

### Dissemination plan

It is the intention of the trial team to disseminate the results of the trial as widely as possible. This is likely to be through publication in a peer-reviewed vascular surgery journal, and also via presentations at National and International Cardiology Conferences. Publication will be in accordance with the CONSORT guidelines. The trial will be registered before randomisation commences. The results will be submitted for presentation at major vascular surgery conferences. It is anticipated that the trial manuscript will be submitted for publication by 2016. The paper will be attributed to the Preconditioning SAVES Group. Individual clinicians involved in the trial will be listed by centre at the end of the trial.

## Discussion

### Strengths

This is the first trial seeking to evaluate the role of remote preconditioning as a protective adjunct in a typical population of elective major vascular surgery patients. It will have sufficient power to detect a reduction in post-operative troponin-positive events, which are known to adversely affect survival following major vascular surgery. The inclusion of a qualitative evaluation of staff and patient experiences with RIPC will also provide formal data on the intervention’s acceptability. The adaptive design allows for evaluation of a combined arm/leg RIPC stimulus should it appear that the arm stimulus alone is insufficient at the interim analysis stage.

### Weaknesses

Ideally, patients randomized to the control arm would receive a sham intervention. Trial staffing is minimal. In the absence of dedicated trial staff at each site to undertake the intervention, the inclusion of a sham intervention was felt to be excessively onerous and likely to adversely impact on trial participation and enrolment by the surgical teams.

## Trial status

Recruitment for the trial began 1 June 2014.

## Abbreviations

AAA: abdominal aortic aneurysm
ACE: angiotensin-converting enzyme
AKI: acute kidney injury
CPAP: continuous positive airway pressure
CT: computed topography
ECG: electrocardiography
EVAR: endovascular aneurysm repair
HRBCRFG: Health Research Board Clinical Research Facility Galway
IPPV: intermittent positive pressure ventilation
ITU: Intensive Therapy Unit
MACE: major adverse clinical event.
NYHA: New York Heart Association
PICO: population, intervention, comparator, outcome
PCI: percutaneous coronary intervention
QALY: quality-adjusted life years
RCT: randomised control trial
RIPC: remote ischaemic preconditioning
